**Version History**

**Original Version Date:** 24AUG2022

**Version Number:** 1.0

**Amendment Date:** 27OCT2022

## **List of Abbreviations**

|         |                                                       |
|---------|-------------------------------------------------------|
| AE –    | Adverse event                                         |
| CRF –   | Case report form                                      |
| CTCAE – | Common terminology and criteria for adverse events    |
| CTRB -  | Clinical Trials Review Board                          |
| EDC -   | Electronic Data Capture                               |
| FDA –   | Food and Drug Administration                          |
| GCP -   | Good Clinical Practice                                |
| HIPAA – | Health information portability and accountability act |
| IACUC – | Institutional Animal Care and Use Committee           |
| PHI –   | Protected health information                          |
| PI –    | Principal investigator                                |
| SAE –   | Serious adverse event                                 |
| SOP -   | Standard operating procedure                          |
| VCCT -  | Veterinary Center for Clinical Trials                 |
| VCOG –  | Veterinary cooperative oncology group                 |
| VMTH -  | Veterinary medical teaching hospital                  |

## Study Summary

|                                       |                                                                                                                                                                                          |
|---------------------------------------|------------------------------------------------------------------------------------------------------------------------------------------------------------------------------------------|
| Title                                 | Intravenous Doxorubicin and Inhaled IL-15 Immunotherapy for Treatment of Lung Metastases                                                                                                 |
| Short Title                           | Inhaled IL-15 plus Doxorubicin                                                                                                                                                           |
| VCCT Study No                         | VCCT-22-009                                                                                                                                                                              |
| Methodology                           | Single-armed study                                                                                                                                                                       |
| Study Duration                        | 1 year                                                                                                                                                                                   |
| Recruitment Duration                  | 1 year                                                                                                                                                                                   |
| Study Center(s)                       | UC Davis VMTH                                                                                                                                                                            |
| Objectives                            | To determine whether preconditioning lymphodepletion with doxorubicin will improve response rates to inhaled IL-15 in dogs with lung metastases. To determine toxicity and tolerability. |
| Number of Subjects                    | 10                                                                                                                                                                                       |
| Diagnosis and Main Inclusion Criteria | Dogs with pulmonary metastasis greater than 1cm.                                                                                                                                         |
| Study Product, Dose, Route, Regimen   | Recombinant Human Interleukin-15 (IL-15), 50ug, inhalation, twice daily for 2 weeks. Doxorubicin (30mg/m2 or 1mg/kg depending on clinician prescription), IV on Day 0.                   |
| Duration of participation             | 98 Days                                                                                                                                                                                  |
| Reference therapy                     | Doxorubicin                                                                                                                                                                              |
| Outcome measures                      | Laboratory test values, physical examination, owner questionnaire.                                                                                                                       |

## **1 Introduction**

This document is a protocol for a dog research study. While companion animal trials are not covered under the US and international standards of Good Clinical Practice (FDA Title 21 part 312 and International Conference on Harmonization guidelines), many of the principles apply. This study is to be conducted according to these standards where applicable and according to government regulations and Institutional research policies and procedures.

### ***1.1 Background***

Previous trials have found that inhaled IL-15 is well tolerated and resulted in durable responses in dogs with metastatic melanoma or osteosarcoma. Analyses of correlative data found that dogs with low lymphocyte counts were more likely to achieve clinical benefit from this therapy. The goal for this study is to determine whether lymphodepletion with doxorubicin prior to initiating inhaled IL-15 might improve response rates in canine patients with metastatic tumors to the lung. The primary endpoints of this study are to determine the safety and preliminary evidence of efficacy for this combination treatment. Toxicity, response, and progression will be evaluated based on modified versions of the VCOG consensus documents for adverse events and RECIST criteria for solid tumors.

### ***1.2 Investigational Agent***

Recombinant Human Interleukin-15 (IL-15) with standard doxorubicin chemotherapy

### ***1.3 Rationale and Risk/Benefits***

Dogs with lung metastases secondary to melanoma or osteosarcoma have a dismal prognosis and response rates to standard chemotherapy are less than 20% for most tumor types. Therefore, these patients are ideal candidates for novel therapies. Previous studies have demonstrated durable responses to inhaled IL-15 in dogs with metastatic osteosarcoma or melanoma without any recognized toxicity. If successful, this trial will provide important evidence in a large animal, outbred model of spontaneous metastasis that preconditioning chemotherapy with doxorubicin treatment followed by immunotherapy with inhaled IL-15 is a safe and potentially effective treatment for dogs with lung metastasis.

## **2 Study Objectives**

### ***2.1 Primary Objective***

To determine whether preconditioning lymphodepletion with doxorubicin will improve response rates to inhaled IL-15 in dogs with lung metastases.

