### ***2.2 Secondary Objective***

Toxicity and tolerability

CONFIDENTIAL

This material is the property of the University of California Do not disclose or use except as authorized in writing by the study sponsor

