#### 3.2 Primary Study Endpoints

Objective response rates based on radiographic response

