#### 3.3 Secondary Study Endpoints

Response duration, toxicity

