#### 3.4 Primary Safety Endpoints

Based on VCOG and known toxicity of doxorubicin. Toxicity will be assessed using client completed forms along with physical exam, temperature, CBC, Chemistry panel, urinalyses.

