##### Start Inhaled IL-15 Therapy:

- Physical examination
- Quality of life assessment form
- 13 mL of blood obtained for CBC, Chem and PBMC's
- CBC evaluated by trials clinician
  - No minimum cell requirements for IL-15 administration, but if clinically unwell from doxo, may delay
- Inhaled IL-15 (50ug) started in hospital followed by 2 hours monitoring (See XXX section for monitoring details)
- 14 days' supply of IL-15, required PPE, IL-15 Administration Diary sent home with owner

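### The primary objective asks about lymphodepletion, but no listed endpoint measures lymphocytes, so the endpoints support a conclusion on the doxorubicin plus IL-15 regimen and not on lymphodepletion

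*Protocol*

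**What the plan says.** The primary objective (Protocol 2.1) is "To determine whether preconditioning lymphodepletion with doxorubicin will improve response rates to inhaled IL-15 in dogs with lung metastases". Section 3.1 repeats this aim and names lymphodepletion as a trial phase, equating it with giving doxorubicin. The rationale in section 1.1 is that, in earlier trials of inhaled IL-15, "dogs with low lymphocyte counts were more likely to achieve clinical benefit from this therapy".

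The remaining objective and the endpoints are:

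- Secondary objective (2.2): "Toxicity and tolerability".
- Primary endpoint (3.2): "Objective response rates based on radiographic response".
- Secondary endpoints (3.3): "Response duration, toxicity".
- Safety (3.4): "Toxicity will be assessed using client completed forms along with physical exam, temperature, CBC, Chemistry panel, urinalyses".
- Outcome measures in the Study Summary: "Laboratory test values, physical examination, owner questionnaire".

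The visit schedule draws blood for a CBC and PBMCs on Day 0 (7.2.2). At the Day 7 visit, where IL-15 starts, it lists "13 mL of blood obtained for CBC, Chem and PBMC's" (7.2.3).

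**The concern.** The objective names a mechanism, while the endpoints measure only the clinical result of the regimen and its toxicity. The CBC appears among the endpoints only as a toxicity assessment. No purpose is given for the PBMC samples, and nothing says what fall in lymphocytes counts as depletion.

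A report that follows the plan would therefore credit lymphodepletion for a positive result, or blame it for a negative one, without showing that it took place. An investigator could still look at the counts afterwards. With 10 dogs, however, a measure or cut-off chosen once the responses are known carries little weight.

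**Working it through.** **1. Objective against endpoints.**

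| Element of the objective | Where it is measured |
|---|---|
| Doxorubicin given | Administration record (10.5) |
| Lymphocytes lowered before IL-15 | No endpoint in 3.2 to 3.4; no definition or threshold anywhere |
| Response rate | 3.2, radiographic response |
| Response duration, toxicity | 3.3 and 3.4 |

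The second row is the link between treatment and the claimed effect, and it is the one left empty.

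**2. Are the data collected?** Section 7.1 schedules CBC and PBMCs on Days 0, 7, 14, 21 and 35. The Day 0 and Day 7 samples bracket doxorubicin and the planned IL-15 start. An absolute lymphocyte count needs a CBC with a differential. The protocol does not say so outright, but the neutrophil criterion in 5.1 suggests that one is done. Section 7.2.3 allows IL-15 to be delayed in a dog that is unwell after doxorubicin, and no repeat CBC at the actual start is scheduled.

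**3. Does the gap touch the primary test?** Inputs from section 8.1: n = 10, null response rate 0.11, target 0.50, one-sided alpha 0.05. With X the number of responders:

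- P(X ≥ 3 | 0.11) = 0.0884, above 0.05.
- P(X ≥ 4 | 0.11) = 0.0178, so the exact rule is 4 or more responses.
- P(X ≥ 4 | 0.50) = 848/1024 = 0.828, consistent with the stated 80% power.

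The test of the regimen against 11% uses no lymphocyte count, so it stands as it is.

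**4. Why the degree of depletion matters for interpretation (illustration only).** Assume, without support in the protocol, that depleted dogs respond at 50% and non-depleted dogs at 11%. With k of 10 dogs depleted, X is the sum of Bin(k, 0.50) and Bin(10 − k, 0.11).

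| Dogs depleted | P(X ≥ 4) |
|---|---|
| 10 | 0.828 |
| 8 | 0.684 |
| 6 | 0.475 |
| 5 | 0.357 |
| 4 | 0.244 |

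Under that assumption, partial depletion alone could make a negative trial likely. The table does not measure the defect: adding an endpoint changes none of these values. The 50% in section 8.1 is also the target for the whole regimen, not for depleted dogs, and the share of dogs depleted is unknown.

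**5. What 10 paired counts can give.** An exact interval for the median change runs from the 2nd to the 9th ordered change. Its coverage is 1 − 2 × P(Bin(10, 0.5) ≤ 1) = 1 − 2 × 11/1024 = 0.979. The 3rd to 8th would give 1 − 2 × 56/1024 = 0.891, which is too low for 95%. So a usable interval exists at this sample size for the change itself.

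**The case against.** **The question can be read at regimen level.** Section 3.1 treats doxorubicin administration as the lymphodepletion phase. Section 8.1 powers the trial for conditioning chemotherapy, and section 1.1 gives the aim as safety and preliminary efficacy of the combination. Comparing the response rate with 11% answers that question whatever the counts. This stands, and it limits the point to what may be concluded about lymphodepletion.

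**The analysis plan may cover it.** How the serial CBC and PBMC data are summarised could be set out in a document not shown. That holds for methods. The objectives and endpoints are fixed in sections 2 and 3 of the protocol, though, and that list omits the measure.

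**Stronger readings are tempting.** A reader might infer that a negative result could not be told apart from failed preconditioning, or that the trial cannot answer its own question. The documents do not support this: the Day 0 and Day 7 counts will exist, and the regimen-level test is intact. A reader might also take the Day 7 rule in 7.2.3 as showing that non-depleted dogs are knowingly treated. That rule says only that no lower limit on cell counts applies. A check for depletion would be an upper limit, so the rule is not evidence of this gap.

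**The new endpoint cannot prove the mechanism.** Doxorubicin is itself chemotherapy, and section 1.3 puts response to standard chemotherapy below 20% for most tumour types. In a single arm, a lymphocyte fall together with responses could still reflect a direct antitumour effect. This stands and belongs in the stated interpretation.

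**Conclusion.** The point holds as a mismatch between objective and endpoints. Sections 2.1 and 3.1 ask about preconditioning lymphodepletion, and sections 3.2 to 3.4 contain no lymphocyte measure. The listed endpoints support a conclusion about the regimen but not about lymphodepletion.

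Its size is modest. The sample size, decision rule and primary test are unchanged, and the missing item is one prespecified endpoint on blood already scheduled. No numerical loss can be attached to it from the documents, since the power figures above rest on assumed subgroup rates. The conclusion assumes that the CBC includes a differential. It is worth correcting before responses are known, because a lymphocyte measure fixed by then is more credible than one chosen afterwards.

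**What to change.** 1. In section 3.3, add a secondary (pharmacodynamic) endpoint: the change in absolute lymphocyte count from the Day 0 CBC, drawn before doxorubicin, to the last CBC before the first IL-15 dose (Day 7 when on schedule). State that the CBC includes a differential.
2. Report the median paired change with an exact confidence interval, and list each dog's count against its response.
3. If a low-count cut-off is used, fix it before responses are known. The protocol gives none, including for the correlative data cited in 1.1.
4. State that the response rate is read as evidence on the regimen. It is read as consistent with a lymphodepletion mechanism only if depletion is shown. This reading is descriptive with 10 dogs and does not exclude a direct doxorubicin effect.
5. For dogs whose IL-15 is delayed, say in advance whether the Day 7 count is used and flagged or one repeat CBC is drawn.

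Separately, sections 6.2 and 7.2.2 give different units for the alternative doxorubicin dose (per kg and per m²). The passages must be reconciled, since the dose bears on how much depletion to expect.

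Cost: one endpoint line and one table. There is no change to the sample size or planned visits, and at most one extra CBC for each delayed dog.

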### ***2.2 Secondary Objective***

Toxicity and tolerability

CONFIDENTIAL

This material is the property of the University of California Do not disclose or use except as authorized in writing by the study sponsor

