### 5.7 *Early Withdrawal of Subjects*

#### 5.7.1 When and How to Withdraw Subjects

Subjects may be withdrawn at the request of the caregiver, due to adverse events, and/or at the investigator's discretion. If any patient becomes increasingly sick, and the quality of life is of concern to the study staff, discussions will occur to determine how to proceed.

The investigator may remove the subject from the trial if their caregivers fail to bring them to scheduled study visits and/or provide data and the caregivers cannot be reached by the study site for 2 weeks. Alternatively, if caregiver cannot consistently give the patient the twice daily inhaled dose of IL-15, they may be removed from the study.

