#### 7.2.5 Follow-up – Visit Day 21 (+/- 3 days)

##### Monitoring, Study Blood & Equipment Return:

- Physical examination
- Quality of life assessment form
- 13 mL of blood obtained for CBC, Chem and PBMCs
- Urinalysis
- Owner returns nebulizer and unused drug to center
- Owner returns completed Daily Drug Administration Diary

CONFIDENTIAL

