### 8.3 *Subject Population(s) for Analysis*

per-protocol/protocol compliant (starting inhaled IL-15)

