### ***10.5 Electronic Data Capture***

Records will be manually entered into a REDCap database. The UCD REDCap will be used to electronically collect QOL surveys from pet owners. Adverse events, protocol deviations, Concomitant Medications, IL-15 and doxorubicin administration will also be databased in REDCap. Basic patient and owner information (ID numbers, e-mails, etc.) will be included to facilitate submission of surveys and collection of AEs.

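### Tolerability is an objective without an endpoint, and the only analysis set leaves out dogs given doxorubicin that never start IL-15, so a tolerability rate computed on it is biased upwards

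*Protocol*

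**What the plan says.** The Study Summary sets the aim "To determine toxicity and tolerability", and Section 2.2 of the protocol repeats it as "Toxicity and tolerability".

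The endpoints follow in Section 3. The primary endpoint (3.2) is radiographic objective response. The secondary endpoints (3.3) are "Response duration, toxicity". Section 3.4 covers safety: "Toxicity will be assessed using client completed forms along with physical exam, temperature, CBC, Chemistry panel, urinalyses". None of them names or measures tolerability.

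Section 8.3 gives one analysis set: "per-protocol/protocol compliant (starting inhaled IL-15"). No all-treated or safety set is stated.

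On incomplete dosing, Section 5.7.1 says that "if caregiver cannot consistently give the patient the twice daily inhaled dose of IL-15, they may be removed from the study". Sections 7.3.3 and 9.4 also allow discontinuation for non-compliance.

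Dosing data are collected. At Day 21 (Section 7.2.5), "Owner returns completed Daily Drug Administration Diary", together with unused drug. Section 10.5 states that "IL-15 and doxorubicin administration will also be databased in REDCap". Appendix II adds a drug accountability log.

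**The concern.** An objective that appears in Section 2 and is gone by Section 3 will be answered after the data are seen, or not at all. Here it also meets an analysis set that is conditional on the treatment having gone well enough to begin.

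The regimen is a combination: doxorubicin on Day 0, then twice-daily nebulized IL-15 from Day 7. A dog that has received doxorubicin and never reaches the first IL-15 dose is the clearest failure of that combination, and it is the dog that Section 8.3 leaves out.

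The toxicity endpoint does not fully cover the gap. Appendix III warns owners that some dogs may be too anxious to accept nebulization. Refused or missed doses need not produce an abnormal laboratory value or a change in health status. The adverse event tables could therefore look clean while the 14-day course was not delivered. What is at stake is whether a statement that the combination was tolerated can be taken at face value when follow-up testing is considered.

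**Working it through.** **1. Objectives against endpoints.**

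| Item | Objective (Summary, 2.2) | Endpoint (3.2 to 3.4) |
|---|---|---|
| Response | yes (2.1) | objective response rate, response duration |
| Toxicity | yes | yes (3.3, 3.4) |
| Tolerability | yes | none |

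**2. Who is in the Section 8.3 set.** The phrase has two readings: the bracket defines the set (dogs that start IL-15), or compliance is a further condition.

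| Dog given doxorubicin on Day 0 | Bracket defines the set | Compliance also required |
|---|---|---|
| Never starts IL-15 | out | out |
| Starts, then cannot be dosed consistently | in | out |
| Completes the 14 days | in | in |

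The first row is lost on both readings. The second row depends on which reading governs, and the protocol does not say. Section 7.2.3 shows that the first row is foreseeable: it allows IL-15 to be delayed in a dog that is unwell after doxorubicin.

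**3. Size.** The protocol states no figure for tolerability, so there is none to reproduce. The sample size in Section 8.1 concerns response and has no bearing here.

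Inputs: N = 10 (Study Summary, 8.1); all 10 are assumed to receive doxorubicin. The protocol gives no rate of non-completion, so k, the number of dogs that do not complete and are left out of the set, is assumed and varied.

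- All-treated rate = (10 − k)/10.
- Rate on the Section 8.3 set = (10 − k)/(10 − k) = 100% for any k.
- Exact (Clopper-Pearson) 95% limits for x of n: the lower limit is the 0.025 quantile of Beta(x, n − x + 1) and the upper is the 0.975 quantile of Beta(x + 1, n − x). When x = n, the lower limit is 0.025^(1/n) and the upper is 100%.

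| k (assumed) | On the 8.3 set | All dogs given doxorubicin |
|---|---|---|
| 1 | 9/9 = 100% (66.4% to 100%) | 9/10 = 90% (55.5% to 99.7%) |
| 2 | 8/8 = 100% (63.1% to 100%) | 8/10 = 80% (44.4% to 97.5%) |
| 3 | 7/7 = 100% (59.0% to 100%) | 7/10 = 70% (34.8% to 93.3%) |

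The gap is 10, 20 and 30 points, or 10 points per omitted dog. The table applies on both readings if the k dogs never start IL-15. If they start and then stop, it applies only on the compliance reading. For k = 2 with one dog of each kind, the bracket reading gives 8/9 = 89%, the compliance reading 8/8 = 100%, and the all-treated rate is 8/10 = 80%.

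**4. Planned doses per dog.** Section 6.2 gives twice daily for 14 days: 2 × 14 = 28.

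**The case against.** A reader might infer that the trial can only find the treatment tolerable. The protocol does not support that.

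- Adverse events are recorded from screening to study completion (9.1) and sought at every caregiver contact (9.2), without restriction to the Section 8.3 set.
- Quality of life forms are completed at every visit, and reported changes in health status become adverse events (9.1).
- Withdrawal for adverse events is foreseen (5.7.1), and a final status form is kept (10.3).

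Poor tolerance of either drug can therefore appear.

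The entry screen is not a fault either. Exclusion 1 and the saline training in Section 7.2.1 test acceptance of the nebulizer before any study drug. A dog that refuses saline was never treated, and requiring that the drug can be delivered is ordinary eligibility. Removal under 5.7.1, 7.3.3 and 9.4 is discretionary and does not erase data already collected.

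It can also be argued that toxicity and tolerability form one safety objective, that owners' ability to nebulize is compliance rather than tolerability, and that Section 8.3 does not say it governs safety reporting. Exact intervals and the handling of dropouts are commonly left to a statistical analysis plan, which is not at hand. At N = 10 the two intervals overlap heavily.

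All of this limits the point without removing it. The protocol lists tolerability beside toxicity and then carries only toxicity into its endpoints. The one analysis set that it fixes omits treated dogs on any reading. That is stated content rather than deferred detail.

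**Conclusion.** The point holds in a limited form. Tolerability is a stated objective with no endpoint, and any tolerability or completion rate computed on the Section 8.3 set is biased towards a favourable result. The bias comes from dogs that receive doxorubicin and never start IL-15 and, if the compliance wording governs, also from dogs that start but cannot be dosed consistently. It does not follow that the result is predetermined, because adverse event recording covers all dogs.

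The size is about 10 percentage points per omitted dog. That rests on 10 dogs all receiving doxorubicin and on assumed numbers of non-completers. If every dog that receives doxorubicin starts and completes IL-15, the two rates coincide.

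**What to change.** In Section 8.3, state that toxicity and tolerability are analysed in all dogs given doxorubicin, and say whether starting IL-15 or compliance defines the set already named there.

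In Section 3.3, add a tolerability endpoint with two parts:

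- the proportion of all dogs given doxorubicin that complete the 14-day IL-15 course, with exact 95% CI, counting dogs that never start or stop early as not completing and giving the reason for each;
- the percentage of the 28 planned IL-15 doses given to each dog, from the diary checked against returned drug.

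This takes a few lines and changes no treatment or visit. The diary, returned drug, accountability log and REDCap administration records are already planned. Section 5.7.2 asks withdrawn owners to return the nebulizer and supplies but does not mention the diary, so the diary should be requested there too. A count of dogs failing nebulizer training is not proposed, because no screen-failure log is described. The remaining cost is that the tolerability figure may look less favourable.
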